**Screening**:						
Demographics		X				
MINI		X		X		
C-SSRS		X		X		
OSU TBI-ID		X		X		
Medical History		X		X		
Treatment History		X		X		
MRI Safety		X		X		
**Recovery Outcomes**:						
DrInC		X		X	X	X
TLFB		X		X	X	X
**Approach Bias (Approach Avoidance Assessment)**:						
Behavioral			X	X		
fMRI			X	X		

*Note*. Columbia Suicide Severity Rating Scale = C-SSRS; DrInC = Drinker Inventory of Consequences; MINI = Mini International Neuropsychiatric Interview for DSM-5; Ohio State University Traumatic Brain Injury Identification Method Short Form = OSU TBI-ID; Timeline Follow-Back = TLFB

## Outcomes and statistical methods

### Primary and secondary clinical outcomes

To evaluate whether AAT significantly improves clinical outcomes relative to Sham, a mixed effects model repeated measures (MMRM) model will be used. The dependent variable in the MMRM model is change from baseline in AUD-related disability (DrInC) at each post-baseline visit (post visit, 3 and 6 mo. follow-up). Predictors in the model will include treatment condition (AAT, Sham), visit (immediately post-training, 3 and 6 mo.), condition by visit interaction term, and baseline DrInC. The primary end point is the post-training visit. The same analytic approach will be applied to the secondary outcome (PDHD). We will model the distribution of percent days heavy drinking to ensure appropriate analysis. All subjects randomized will be included in the intent-to-treat analysis. Depending on the type of missing data, the appropriate statistical approach (e.g., multiple imputation) will be determined. Sensitivity analyses will be used to explore the impact of missing data.

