**Methods:**

One hundred thirty-six Veterans currently receiving outpatient treatment for AUD will be recruited for this randomized controlled trial with parallel group assignment. Participants will be randomized to either 6 weeks of AAT (n = 68) or Sham (n = 68) training in conjunction with usual care. Assessments will occur at baseline and 6 weeks, 3 months, and 6 months post-baseline. Primary outcome variables will include functional consequences of drinking. Secondary outcome variables will include alcohol consumption, and behavioral indicators of alcohol approach bias. A subset of participants (n = 51) will also complete functional magnetic resonance imaging (fMRI) to assess neural response during an alcohol approach bias assessment.

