### Sample size

Sample size determinations for the functional outcomes were made with a series of power calculations conducted using RMASS power calculation software for longitudinal mixed models. Parameters entered into the calculation included an effect size of d = 0.6 [32], 4 time points, attrition ranges between 20 and 25% based on rates in a prior VA-based clinical trial with a similar sample [47], and α = 0.05. Under the most conservative retention rate, we will need to enroll 136 participants to achieve 80% power. Sample size determinations for imaging outcomes were made using R:WebPower software for analysis of variance for a treatment group x time interaction term. Parameters entered into the calculation included an effect size of d = 0.80, 2 time points, and attrition as above with α = 0.05. We will need a sample of n = 51 to achieve 80% power to detect a treatment group x time effect on the regions encompassed within our a priori mask.

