### Allocation

Randomization will occur during the second visit after eligibility criteria have been confirmed. Randomization sequences will be generated by the study quantitative psychologist, who is not involved in recruitment or data collection, using a computer-generated randomization sequence, using R (*Base* package*)* [50] and administered through RedCAPs randomization function. Randomization will occur without the ability to predict a participant’s allocation before randomizing. Randomization will be blocked (block size = 4 participants; 34 blocks total) and stratified by age category (2 strata: < 40 vs. > = 40 years old) given that age is known predictor of AAT response [31]. The study design will be double-blind, i.e., the participant, assessor, and PIs will be masked to the treatment condition for the duration of the trial with no planned unblinding. Within each stratum, participants will be divided into four groups, i.e., 2 treatment conditions (AAT vs. Sham) X 2 image set orders for Pre and Post Assessment AAT (AB vs. BA), with an allocation ratio of 1:1:1:1. Each computer program corresponding to each of the 4 conditions will be blinded such that the coordinator will not know the nature of the program. Assessors will not deliver the intervention. The patient and assessor will each rate their prediction regarding the patient’s assigned treatment condition after each assessment to check the success of blinding.

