### Secondary behavioral outcomes

To assess change in alcohol-related approach bias and cognitive performance, we will use the Approach Avoidance Assessment approach bias score (reaction time in seconds; alcohol-push minus alcohol-pull). To determine whether AAT engages the target as hypothesized (i.e., improving approach bias), we will analyze the effect of AAT versus the Sham group in a mixed effects model repeated measure approach as in Aim 1.

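### Randomisation is stratified by age, but the primary DrInC model as stated leaves the age stratum out: a small efficiency loss if age is prognostic, fixable for one degree of freedom

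*Protocol article*

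**What the plan says.** **Allocation section.** Randomisation is in blocks of 4, stratified by age category (<40 versus >=40 years). The reason given is "given that age is known predictor of AAT response". Within each stratum, participants are spread equally over four groups, formed by crossing the two treatments with "2 image set orders for Pre and Post Assessment AAT (AB vs. BA").

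**Primary and secondary clinical outcomes section.** The dependent variable is change from baseline in DrInC at three post-baseline visits, with the post-training visit as the primary end point. The predictors are treatment condition, "visit (immediately post-training, 3 and 6 mo.), condition by visit interaction term, and baseline DrInC". Percentage of heavy drinking days is to be analysed in the same way, with its distribution still to be modelled.

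**Secondary behavioral outcomes section.** Approach bias is to be analysed with a "mixed effects model repeated measure approach as in Aim 1". Neither age nor picture-set order is named.

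**Sample size section.** The inputs are "effect size of d = 0.6 [32], 4 time points, attrition ranges between 20 and 25" percent, and the conclusion is that "we will need to enroll 136 participants to achieve 80% power". The abstract gives the arms as "6 weeks of AAT (n = 68) or Sham (n = 68) training".

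**The concern.** Blocking within age strata makes the two arms nearly equal in age mix, so age contributes little to the chance difference between arms. A model without age does not know this. It leaves any age-related spread in the residual and computes the standard error as if age could still differ freely between arms. Where age is prognostic, that standard error is larger than the true sampling variability, the test rejects too rarely under the null, and power is lower than the same data would give with the stratum in the model.

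The article does more than stay silent on covariates. It names one (baseline DrInC) and leaves out the factor the trial chose to stratify on. At stake is efficiency in a single-site trial planned at 80% power with up to 25% attrition.

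Picture-set order raises the same question in a weaker form. Any difference between sets A and B would add to the residual of the approach-bias change score unless order is modelled.

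**Working it through.** **Inputs from the article.** 136 randomised, 68 per arm; attrition up to 25%; alpha 0.05 (taken as two-sided, since sidedness is not stated); d = 0.6; target power 80%. Completers at 25% attrition: 136 × 0.75 = 102, or 51 per arm.

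**Input the article does not give.** R², the share of DrInC-change variance left after baseline adjustment that the age stratum explains. Assumed range: 0 to 0.20.

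**Step 1: the plan's own figure.** A simple two-group comparison needs 2 × (1.96 + 0.84)² / 0.6² = 43.6, so 44 per arm. Then 88 / 0.75 gives 118, not 136. The plan used longitudinal software, whose answer also depends on the within-person correlation and the contrast, and neither is stated. For a linear trend over 4 equally spaced times reaching 0.6 SD, with equal correlation ρ between times, the requirement is 78.5 × (1 − ρ) per arm. At ρ of about 0.35 that is 51 per arm, 102 completers and 136 enrolled. So 136 is attainable but cannot be verified, and it is not disputed here. The steps below are calibrated to 80% power with 51 per arm when age does not matter, so the expected test statistic is 1.96 + 0.84 = 2.80.

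**Step 2: formulas (normal approximation, one visit).**
- Standard error without age relative to with age: 1/√(1 − R²).
- True type I error without age, balance fully kept: 2[1 − Φ(1.96/√(1 − R²))].
- The same after 25% random dropout. Dropout restores about a quarter of the age variation between arms, so 1 − R² becomes 1 − 0.75R².
- Power with age: Φ(2.80/√(1 − R²) − 1.96).
- Power without age, balance kept: Φ((2.80 − 1.96)/√(1 − R²)).

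**Step 3: results.** Gains are taken before rounding.

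| R² | SE too large by | Type I error, balance kept | Type I error, 25% dropout | Power without age | Power with age | Gain (points) |
|---|---|---|---|---|---|---|
| 0 | 0% | 5.0% | 5.0% | 80.0% | 80.0% | 0 |
| 0.02 | 1.0% | 4.8% | 4.8% | 80.2% | 80.8% | 0.5 |
| 0.05 | 2.6% | 4.4% | 4.6% | 80.6% | 82.0% | 1.4 |
| 0.10 | 5.4% | 3.9% | 4.2% | 81.2% | 84.0% | 2.7 |
| 0.20 | 11.8% | 2.8% | 3.4% | 82.7% | 87.9% | 5.3 |

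**Step 4: check by simulation.** The simulation used 8,000 runs, 136 randomised in stratified blocks of 4, 25% random dropout, one visit, and 60% aged 40 or over (assumed). Power without versus with age was 79.5% versus 80.0% at R² = 0.02, 78.7% versus 80.0% at 0.05, 79.3% versus 82.6% at 0.10, and 80.6% versus 86.9% at 0.20. Type I error at R² = 0.20, with dropout included, came out between 3.0% and 3.6% across simulations, around the 3.4% in the table.

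**Step 5: which R² is plausible?** With two equal strata an age gap of g within-stratum SDs gives R² = (g²/4)/(1 + g²/4).
- R² = 0.02 needs g of about 0.29.
- R² = 0.10 needs g of about 0.67.
- R² = 0.20 needs g = 1.0.

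The last two exceed the planned treatment effect of 0.6. If age only modifies the effect, say 0.3 SD in one stratum and 0.9 SD in the other, the average age gap over both arms is (0 + 0.6)/2 = 0.3 SD. R² is then about 0.02.

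**The case against.** Most of the case on the other side concerns size and certainty, and much of it stands.

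- **The loss is conditional.** It needs age to explain DrInC change after baseline DrInC, and the article gives no evidence on that. Calling age a predictor of response to the training may mean that it modifies the effect rather than that it is prognostic. On that reading the loss in the illustration is under one power point.
- **It is not a validity problem.** A reader might infer a must-fix error or a trial that misses its 80% power. Neither follows. The test errs on the conservative side, the estimate is not biased by the omission, and d = 0.6 is not described as age-adjusted.
- **Dropout softens the conservatism.** Type I error at R² = 0.20 is about 3.4%, not the 2.8% obtained when balance is assumed to survive attrition.
- **Picture-set order is weaker still.** A reader might infer the same loss for the approach-bias model. The two sets are matched by design, order is balanced across arms, and the article gives nothing from which to size a difference between them. Approach bias also has only one post-baseline measurement, so the three-visit DrInC model cannot carry over literally, and that section does not fix its covariates.
- **Extensions to the imaging model or an age-by-treatment term** are matters of preference and do not follow from this mismatch.
- **The list may not be exhaustive.** The article is condensed, and a full analysis plan may add the stratum. This lowers the severity. It does not remove the point, because the article states a specific set of predictors and omits the one stratification factor.

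**Conclusion.** The point holds as a low-severity improvement. The stated primary model does not match the stated randomisation, because the age stratum is used to allocate and then not named in the analysis. If age is prognostic for DrInC change beyond baseline, with R² between 0.02 and 0.10, the standard error is about 1% to 5% too large and about 0.5 to 3 power points are forgone. At R² = 0 nothing is lost. At R² = 0.20 the loss would be about 5 to 6 points, but that requires an age gap of a full SD, which nothing in the article supports.

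These figures assume a linear model at a single visit, a two-sided test, 51 completers per arm and dropout at random. They do not carry over directly to heavy-drinking days if that outcome is fitted with a non-linear model. They are no evidence against the sample size of 136.

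**What to change.** State in the analysis section that the age stratum used at randomisation (<40, >=40) enters the mixed model for DrInC as a prespecified fixed effect, and likewise the models for percentage of heavy drinking days and approach bias. Picture-set order (AB, BA) may be added to the approach-bias model as a minor, optional term.

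The cost is one sentence and one degree of freedom, or two in the approach-bias model if set order is included. Age is already recorded at baseline and set order is part of the allocation, so no new data are needed. The wording should be fixed before treatment codes are broken, since a covariate added after results are seen would look data-driven.

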It is important to address potential limitations and possible mitigation approaches associated with conducting the proposed study. The main challenges include treatment adherence, participant retention, and study completion since dropout rates for addiction treatments are high, especially in comorbid populations [58, 59]. As attrition rates are anticipated to range between 20 and 25%, participants will be overrecruited to ensure the study is well powered to examine treatment effects. The treatment protocol includes 12 sessions, administered twice a week for 6 weeks, which can be demanding for participants who are also receiving concurrent clinical care. AAT treatment sessions will therefore be made as convenient as possible by allowing in-person or remote appointments, depending on participant preference, in order to reduce participant burden. Procedures will also be put in place to remind participants of their appointments and provide opportunities to easily reschedule missed treatment sessions. To support retention, participants are asked to provide mobile phone numbers, home addresses, and a secondary phone contact to ensure treatment reminders are received in a timely manner. Participants are compensated for study participation after completion of each follow-up appointment. Task-based adherence data will be collected during the computerized treatment sessions to assess if participants are engaging sufficiently in treatment sessions.

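### The MMRM gives baseline DrInC one slope for all three visits; a baseline-by-visit term would be a near-free gain for the 3- and 6-month contrasts and matters little at the primary visit

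*Protocol article*

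**What the plan says.** The protocol article, under Primary and secondary clinical outcomes, models "change from baseline in AUD-related disability (DrInC) at each post-baseline visit" at three visits: post-training, 3 months and 6 months. The listed predictors are condition, visit, "condition by visit interaction term, and baseline DrInC". The treatment effect may therefore differ by visit, while baseline appears once, as a main effect.

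The same section fixes the primary time point: "The primary end point is the post-training visit". It leaves the missing-data method open, with multiple imputation as an example, and adds: "Sensitivity analyses will be used to explore the impact of missing data". PDHD is to follow the same approach, with its distribution still to be modelled.

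The Sample size section assumes "an effect size of d = 0.6" and "attrition ranges between 20 and 25" percent. The Discussion notes that "dropout rates for addiction treatments are high, especially in comorbid populations".

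**The concern.** Follow-up DrInC scores cover 30 days and are taken at about 6 weeks, 3 months and 6 months. A baseline score plausibly predicts the 6-week score better than the 6-month one. If so, a single slope is too shallow at the post-training visit and too steep at 6 months.

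Two things could follow. The baseline adjustment removes less variance than it could. And if the participants still observed differ between arms in baseline severity, a wrong slope converts that difference into a spurious treatment difference. Likelihood methods handle dropout that depends on baseline only when the mean model is right at each visit.

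PDHD has a further reason for unequal slopes. The baseline TLFB spans 90 days and later ones span the time between interviews. Training takes 6 to 10 weeks, so the 3-month window is roughly 13 − 10 = 3 to 13 − 6 = 7 weeks, against about 13 weeks for the 6-month window.

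**Working it through.** **Inputs from the article.** 68 per arm, d = 0.6, attrition 20 to 25%, three post-baseline visits, predictors as listed.

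**Assumed, shown as ranges.** Baseline-to-visit correlations at post, 3 and 6 months, and how dropout depends on baseline. The article gives neither.

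**The plan's own figure.** The stated N of 136 cannot be reproduced exactly, because the within-person correlation used in RMASS is not given. A simple two-sample calculation gives 2(1.96 + 0.84)²/0.6² ≈ 43.6, so 44 per arm and 88 in total; 88/0.75 gives 118. A linear-trend repeated-measures formula with 25% attrition gives 136 at an assumed correlation of 0.35, and 167 to 105 over correlations of 0.2 to 0.5. The present point does not alter N.

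**Precision.** Maximum-likelihood MMRM with unstructured covariance, fitted with a common slope and with visit-specific slopes. Entries are the excess variance of the common-slope model. Rows marked * are empirical variance ratios from 1,500 simulated trials with 68 per arm and 12/18/25% cumulative missingness. The other rows are squared SE ratios from a run with N = 200,000 and about 25% dropout completely at random (for example 1.0285² = 1.058).

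| Correlations (post/3/6 mo) | Post | 3 mo | 6 mo |
|---|---|---|---|
| 0.6/0.6/0.6 | 0% | 0% | 0% |
| 0.6/0.5/0.4 | 0.8% | 0.2% | 2.1% |
| 0.6/0.45/0.3* | 0.6% | 0.1% | 3.3% |
| 0.7/0.55/0.4 | 1.4% | 0.8% | 5.8% |
| 0.7/0.4/0.2* | 3.1% | 3.5% | 14.8% |
| 0.8/0.5/0.2 | 1.9% | 7.0% | 28.3% |

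The post visit suffers little because the fit weights it most. Its residual variance, 1 − ρ², is the smallest: in the last row 0.36 at post against 0.96 at 6 months. The common slope there is 0.719, nearer to 0.8 than to 0.2.

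**Bias.** To a first approximation the error in the contrast at visit v is (β_v − b)·Δx. Here β_v is the true slope, b the common slope, and Δx the AAT-minus-Sham gap in mean baseline among those still observed. It vanishes if slopes are equal (β_v = b) or if dropout acts alike in both arms (Δx = 0). Simulated bias of the common-slope model, in SD:

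| Correlations | Dropout dependence on baseline, per SD | Post | 3 mo | 6 mo |
|---|---|---|---|---|
| All sets in the N = 200,000 run | same in both arms | within ±0.006 | within ±0.006 | within ±0.006 |
| 0.6/0.5/0.4 | one arm only | −0.007 | 0.003 | 0.023 |
| 0.6/0.5/0.4 | opposite, log-odds ±0.7 | −0.014 | 0.012 | 0.051 |
| 0.7/0.55/0.4 | one arm only | −0.008 | 0.010 | 0.038 |
| 0.7/0.55/0.4 | opposite, log-odds ±0.7 | −0.015 | 0.024 | 0.082 |
| 0.8/0.5/0.2 | one arm only | −0.007 | 0.032 | 0.089 |
| 0.8/0.5/0.2 | opposite, log-odds ±0.7 | −0.014 | 0.069 | 0.184 |
| 0.6/0.45/0.3* | opposite, log-rate ±0.3 | −0.008 | 0.009 | 0.042 |
| 0.7/0.4/0.2* | opposite, log-rate ±0.6 | −0.024 | 0.051 | 0.146 |

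With visit-specific slopes every bias was within about 0.006 SD of zero.

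Check against the formula, steep case with opposite dependence: b = 1 − 0.275 = 0.725 and β at 6 months is 0.2. A bias of 0.184 then implies Δx = 0.184/(0.2 − 0.725) ≈ −0.35 SD. That is in line with the 0.39 SD gap found at 6 months in the ±0.6 log-rate setting.

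**Power at 6 months** (N = 136, true effect 0.6 SD, 600 trials, common against visit-specific slopes). Dropout completely at random: 0.91 against 0.915 (0.7/0.55/0.4) and 0.80 against 0.885 (0.8/0.5/0.2). Opposite dependence: 0.80 against 0.90 and 0.50 against 0.875.

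**The case against.** - **The predictor list need not be exhaustive.** The article is condensed, and a fuller plan may contain the interaction. This stands as a reason to ask for confirmation. It does not remove the point, because the article spells out the visit interaction for treatment and gives none for baseline.
- **The primary result is safe.** This stands. A reader might infer from a fault in the primary model that the primary comparison is compromised, but the article makes post-training the primary visit, and the effect there is very small.
- **Dropout related to severity is not enough for bias.** This stands. A reader might take the Discussion's remark on high dropout as evidence of bias. That remark concerns overall dropout in comorbid populations; it says nothing about baseline DrInC or a difference between arms. Participants and assessors are masked and Sham is matched for number of sessions, so opposite dependence is a stress case. With dependence in one arm only, the 6-month bias roughly halves.
- **Multiple imputation would remove the bias.** In a check with sequential imputation from arm, baseline and earlier visits, all biases of the common-slope contrast were within 0.010 SD of zero. The bias claim is therefore confined to direct likelihood. The article has not committed to either method.
- **Decay is assumed.** This stands. With up to 10 weeks allowed for training, post and 3 months may be only weeks apart, so a sharp fall in correlation between them is not assured. With flat correlations nothing is lost.
- **The PDHD model is not fixed.** This stands; the DrInC figures do not carry over to it.

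**Conclusion.** The plan as written uses one baseline slope for three visits, and visit-specific slopes are the better choice. This is a minor refinement, not an error that puts the primary comparison at risk.

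At the post-training visit the cost is about 0.5 to 3% in variance, with bias of at most about 0.02 SD, or 0.024/0.6 = 4% of the planned effect, in the least favourable case. At 6 months the variance excess is about 2 to 6% under mild to moderate decay and 15 to 28% under steep decay. Bias in the 3- and 6-month contrasts needs three things together: slopes that change over visits, dropout that depends on baseline differently by arm, and a direct-likelihood analysis. Under opposite dependence the 6-month bias was 0.04 to 0.18 SD, or 7 to 31% of 0.6.

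All these sizes rest on assumed correlations and dropout models. The documents establish neither decay nor differential dropout.

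**What to change.** Add baseline DrInC by visit to the MMRM before unblinding, or confirm that the full plan already includes it. An equivalent route is to model baseline as a response with a common mean across arms and unstructured covariance, which yields visit-specific slopes. If a repeated-measures model is kept for PDHD, add baseline PDHD by visit there.

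The cost is two degrees of freedom from about 136 × 0.75 = 102 completers, with no new data and no change to N. With flat correlations and dropout completely at random the added term carried no SE penalty (ratio 1.000). When dropout differed by arm the penalty was about 1% at most. The gain is chiefly in the follow-up contrasts, which carry the evidence on durability.
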